## Methods

### Study Overview

Project Caboodle! is an exploratory 2-year study to obtain both quantitative and qualitative data regarding the acceptability and feasibility of biological specimen self-collection and return from sexually active HIV-negative or unknown status MSM aged 18 to 34 years residing in the United States or dependent areas. In Phase 1, we will send 100 participants a box containing instructions and materials for self-collecting and potentially returning a finger-stick blood sample (for HIV testing), pharyngeal swab, rectal swab, and urine specimen (for gonorrhea and chlamydia testing), and hair sample (to assess adequacy for potential PrEP adherence monitoring in the future). Specimen return is not incentivized, and participants can choose to mail back all, some, or none of these 5 specimens. In Phase 2, we will conduct individual in-depth interviews using a video-based teleconferencing software (VSee) with 32 participants from Phase 1 to examine attitudes toward and barriers to self-collecting and returning each type of specimen.

Guided by the theoretical constructs of the Information-Motivation-Behavioral skills (IMB) model [88,89], the specific aims of our study are as follows:

*Aim 1:* Explore the acceptability and feasibility of self-collecting at home and returning by mail all, some, or none of the following biological specimens: (1) finger-stick blood sample, (2) pharyngeal swab, (3) rectal swab, (4) urine specimen, and (5) hair sample, among 100 sexually active HIV-negative or unknown status US MSM (aged 18 to 34 years, 50 black and 50 white including those of Hispanic ethnicity) recruited through social media platforms.*Aim 2:* Collect qualitative data via individual in-depth interviews conducted using VSee from 2 subsamples of 16 MSM each, including participants who (1) returned all 5 specimens and (2) returned some or no specimens to examine attitudes toward and barriers to completing various study activities.

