### Phase 1 Procedures

Registered participants will be sent an email containing a link to the baseline survey, programmed in Qualtrics. The survey will include questions pertaining to the following domains— *demographic characteristics:* data on age, race and ethnicity, educational level, sexual orientation, employment status, history of incarceration, history of homelessness, health insurance coverage, and access to health care will be collected [94]; *HIV testing history:* participants will be asked about whether they have ever been tested for HIV, the time frame of their most recent test, the location of their most recent test, and their annual frequency of testing or their reasons for never testing [81,86,94]; *home-based HIV testing:* data will be collected on whether participants have ever used a commercially available self-collection kit (eg, Home Access HIV-1 Test System and OraQuick In Home HIV Test) and the type of test kit they have used or their reasons for never using a self-collection kit; *PrEP knowledge, use, and intentions:* questions will be adapted from recent studies of PrEP attitudes among MSM [95-97] to collect data on whether participants have heard about PrEP, are currently using PrEP, their previous use of PrEP, reasons for never using or discontinuing PrEP, access to PrEP, and intentions for future use of PrEP; *bacterial STI testing history:* participants will be asked about whether they have ever been tested for bacterial STIs, the time frame of their most recent tests, the location of their most recent tests, different anatomical sites at which they have been tested, whether they have ever been diagnosed with any STIs in the past, and if so, whether they received treatment or their reasons for never testing [98,99]; *sexual behavior:* data will be collected on relationship status, the number of sex partners with whom participants have had condom-less anal or oral sex in the past 3 months, and whether any of those partners were known to be positive for HIV or other STIs [100,101]; *knowledge of transmission and prevention of HIV and other STIs:* the 27-item STD-KQ will be used to assess participants’ knowledge about different STIs [92]; *perceived risk of contracting HIV and other STIs:* participants will be asked to indicate how concerned they are about contracting HIV and other STIs on a 10-point scale ranging from not concerned at all to very concerned [102]; *experiences with medical care:* the Group-Based Medical Mistrust Scale will be used to assess participants’ previous experiences of racial discrimination and feelings of discomfort and suspicion they might have toward health care personnel and medical treatments [103]; *theoretical willingness and perceived ability to self-collect and return biological specimens:* Likert-item questions will be used to assess participants’ intentions to self-collect and return each of the 5 different types of biological specimens similar to previous studies [81,90], as well as their confidence to complete these activities using simple step-by-step written instructions accompanied by color images; *substance use and psychological distress:* participants will be asked about their alcohol, tobacco, and other drug use in the past 6 months and to self-report depressive symptomology on the revised Center for Epidemiologic Studies Depression Scale [104]. The baseline survey will take approximately 30 min to complete, and participants will receive an incentive of US $40 in the form of an Amazon gift card.

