
After participants have been sent the original email containing a link to the baseline survey, they will receive up to 3 reminders at weekly intervals using their preferred communication method indicated during registration (email, phone call, or text). The final reminder will advise participants that noncompletion of the survey within the next 7 days will suggest that they are no longer interested in continuing, unless they contact the study staff and ask for an extension. They will be also be advised that they will no longer qualify to receive a specimen self-collection box in the mail after that time has lapsed. Participants who do not complete the baseline survey within 7 days of receiving the final reminder (ie, by the end of 4 weeks after the original email has been sent) will be thanked for their interest in the study and emailed information about the CDC HIV Risk Reduction Tool website.

Participants who complete the baseline survey will be shipped a box containing instructions and materials for self-collecting and potentially returning 5 different types of biological specimens (ie, a finger-stick blood sample, pharyngeal swab, rectal swab, urine specimen, and hair sample). Each box and its components will be affixed with a unique identification sticker to enable specimen identification upon return. Boxes will be shipped from the University of Michigan School of Nursing (UMSN) in Ann Arbor using United Parcel Service (UPS) in plain unmarked packaging, and their delivery will be tracked by the study staff on an ongoing basis. Contents of the box will include the following:

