### Phase 1 Analytic Plan

Descriptive statistics (means, medians, and interquartile ranges for continuous variables, and counts and proportions for categorical variables) will be used to characterize the demographic and behavioral characteristics of the sample (including HIV and bacterial STI testing history) using software for quantitative data analysis (SAS). Analyses paralleling the IMB model include— *Information:* (1) Proportions of participants who are aware of commercially available self-collection kits for home-based HIV testing will be estimated, (2) Scores for the knowledge of transmission and prevention of HIV and other STIs will be formulated for each participant, and (3) Variations in knowledge levels across categories of selected characteristics will be assessed using chi-square tests for homogeneity; *Motivation:* (1) Frequency distributions of participants’ theoretical willingness to self-collect and return each of the 5 different types of biological specimens will be plotted, (2) Proportions of each type of specimen actually returned will be calculated and compared with theoretical willingness using Fisher exact tests across categories of selected characteristics (eg, age, race and ethnicity, educational level, sexual orientation, HIV and bacterial STI testing history, relationship status, sexual behaviors, experiences with medical care, substance use, and psychological distress), and (3) Reasons for not returning certain types of specimens will be tabulated, including manually reviewing and reassigning open-ended responses to appropriate pre-specified options; and *Behavioral skills:* (1) Frequency distributions of participants’ perceived ability to self-collect and return each of the 5 different types of biological specimens will be plotted and (2) Proportions of each type of returned specimen that are deemed adequate for actual laboratory testing (for HIV, gonorrhea, and chlamydia) and potential laboratory testing (for PrEP drug levels) will be calculated. Frequencies and proportions of positive and negative HIV, gonorrhea, and chlamydia test results and linkage to care statistics will also be aggregated.

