## Discussion

### Principal Findings

Project Caboodle! seeks to explore the acceptability and feasibility of self-collecting at home and returning by mail a bundle of 5 different types of biological specimens by young sexually active MSM residing in the United States. The potentially reduced time, expense, and travel associated with this strategy could facilitate a wider implementation of HIV and bacterial STI testing algorithms, as well as PrEP adherence monitoring in this high-risk group. Although some recent studies have focused on the acceptability of self-collecting and returning individual specimens for HIV or other STI testing (as opposed to a bundle) [75-87], none have incorporated PrEP adherence monitoring using hair samples. As hair is nonbiohazardous, easy-to-ship, and stable at room temperature, this specimen is particularly adaptable to self-collection. As PrEP moves from clinical trials into routine practice, these preliminary data can guide the future development of remote monitoring strategies for MSM. Our study will fill a critical gap in knowledge regarding feasibility by comparing the theoretical willingness and perceived ability to self-collect each of the 5 different types of biological specimens with the proportions of specimens actually returned and their adequacy for laboratory testing, respectively. High levels of theoretical willingness may overstate the actual rates of self-collection and return of certain specimens (eg, finger-stick blood, which is invasive to collect) because intentions do not always translate into behavior [107,108]. Obtaining this information is important, as naively assuming that positive intentions would translate into meaningful action could result in an inefficient deployment of limited resources in larger research studies and public health programs. Finally, gathering qualitative data on attitudes toward and barriers to self-collecting and returning both invasive and noninvasive specimens is critical to developing novel prevention interventions for MSM, with the ultimate goal of reducing their disproportionate burden of HIV and other STIs.

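### The Fisher exact comparison of specimen return with stated willingness is ambiguous, and no reading of it gives a paired test of the gap between them

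*Protocol article*

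**What the plan says.** The Phase 1 Analytic Plan (Motivation, item 2) states that the proportion of each specimen type returned will be "compared with theoretical willingness using Fisher exact tests across categories of selected characteristics". It names no paired method.

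Three other places in the article settle what kind of data this test will meet.

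- Phase 1 Procedures: willingness is measured at baseline for each of the five specimens ("Likert-item questions will be used to assess" it). No cut from the Likert scale to willing or not willing is given.
- Phase 1 Procedures: "Participants who complete the baseline survey will be shipped a box". Every man who can return a specimen has therefore already answered the willingness items. Under Phase 1 Outcomes, return is a yes/no outcome for each specimen within 6 weeks of box delivery.
- Study Overview: there is a single cohort ("In Phase 1, we will send 100 participants a box"), made up of "50 black and 50 white including those of Hispanic ethnicity", with no separate comparison group.

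Principal Findings, in the Discussion, says why the comparison is made: "High levels of theoretical willingness may overstate the actual rates of self-collection and return of certain specimens". The article presents this comparison as filling a critical knowledge gap about feasibility.

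**The concern.** Asking whether willingness overstates return means asking whether two proportions measured on the same men differ. The information lies in the discordant men: those who said they would return a specimen and did not, and those who said they would not and did. Fisher's exact test as named does not use the data in that way.

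The sentence also does not say which table the test is applied to. Different analysts could build different tables in good faith and reach opposite conclusions from the same 100 men. What is at stake is the inference on the contrast that the article itself puts forward as its contribution. The data collected are not affected.

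**Working it through.** **Inputs from the article.** n = 100 men, 50 in each race group; willingness at baseline and return within 6 weeks, both on the same men. The article gives no expected rates, alpha or power for this comparison, so there is no figure of its own to reproduce. Every table below is an assumption chosen to show how the tests behave; p-values are two-sided and set against 0.05.

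**Notation.** For one specimen, a = willing and returned, b = willing and not returned, c = not willing and returned, d = neither; n = a + b + c + d.

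- Gap = (a + b)/n − (a + c)/n = (b − c)/n.
- Paired SE = √[(b + c) − (b − c)²/n] / n.
- SE if treated as independent samples = √[p_w(1 − p_w)/n + p_r(1 − p_r)/n].
- Exact McNemar: binomial test of b against c with probability 1/2.

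**Reading 1: cross-table of willing by returned.** Fisher on (a, b; c, d) tests whether return depends on willingness.

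- 45/45/5/5: willing 90%, returned 50%, gap (45 − 5)/100 = 40 points. Half of the willing (45/90) and half of the unwilling (5/10) return, so there is no association: Fisher p = 1.0. Exact McNemar p = 4e-9.
- 88/2/2/8: willing 90%, returned 90%, gap 0. Fisher p = 1e-8; exact McNemar p = 1.0.

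This reading can mislead in both directions about the gap.

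**Reading 2: the two proportions stacked as separate groups.** Fisher on (a + b, c + d; a + c, b + d) targets the right contrast but counts 100 men as 200.

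- 50/10/0/40: willing 60%, returned 50%, gap 10 points.
  - Stacked Fisher p = 0.20; exact McNemar p = 2 × (1/2)^10 = 0.002.
  - Independent SE = √(0.60 × 0.40/100 + 0.50 × 0.50/100) = √0.0049 = 7.0 points.
  - Paired SE = √(10 − 100/100)/100 = √9/100 = 3.0 points.
- 25/8/1/16, one race stratum of 50: willing 66%, returned 52%, gap 14 points. Stacked Fisher p = 0.22; exact McNemar p = 0.039; SE 9.7 against 5.7 points.
- 45/45/5/5 again: stacked Fisher p = 5.5e-10, with both SEs 5.83 points. A very large gap is still found.

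Simulation (4,000 data sets per setting):

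| Setting | Within-person correlation | Stacked Fisher | Exact McNemar |
|---|---|---|---|
| Power, 90% v 80%, n = 100 | 0 | 45% | 42% |
| Power, 90% v 80%, n = 100 | 0.3 | 43% | 58% |
| Power, 90% v 80%, n = 100 | 0.6 | 41% | 85% |
| Power, 90% v 80%, n = 50 | 0.6 | 10% | 35% |
| Type I error, 80% v 80%, n = 100 | 0 | 3.0% | about 3% |
| Type I error, 80% v 80%, n = 100 | 0.3 | 1.0% | about 3% |
| Type I error, 80% v 80%, n = 100 | 0.6 | 0.1% | about 3% |

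With positive correlation the stacked form is conservative and its power does not benefit from the pairing. Inflation to 8.1% appeared at a correlation of −0.5 with 50% margins, an unlikely pattern for willingness and return.

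**Reading 3: return compared between categories, such as black and white men.** Each man is counted once and Fisher is valid. The comparison is then of return between groups, and nothing tests willingness against return.

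**The case against.** The strongest reply is that the sentence speaks of categories of characteristics and lists them, which fits the third reading, where Fisher is sound. That stands as a possible reading. It does not rescue the plan, because the sentence also says return is compared with willingness, and on this reading that comparison has no test.

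The cross-table is not meaningless either. Whether willing men return more often than unwilling men is a reasonable question about intention and behaviour, and Fisher answers it. It is a different question from overstatement.

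A reader might infer that the planned test can never answer the overstatement question. The documents do not support that: the stacked form addresses the right proportions with the wrong variance. Nor may the p = 1.0 of the cross-table and the missed modest gaps of the stacked form be added together as faults of one test. They belong to different readings, and only one could be the planned analysis.

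A reader might also infer that the plan omits a promised test of perceived ability against specimen adequacy. The Discussion promises a comparison, and the analytic plan supplies the distribution of the one and the proportions of the other. A descriptive comparison meets that promise, so it is no fault.

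Finally, the study is exploratory, with no primary hypothesis or decision rule tied to this test, and the willingness distributions and return proportions will be reported whatever test is used. The gap will therefore be visible. This lowers the severity but does not remove the mismatch.

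**Conclusion.** The point holds as a mismatch between a named test and the design, made worse by an ambiguous sentence. That the data are paired follows from the article's own procedures and needs no assumption. On each of the three readings the named test either answers another question or ignores the pairing.

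The size depends on the reading and on rates the article does not give. Under the cross-table reading the p-value carries no information about the gap. Under the stacked reading the likely harm is lost power for modest gaps, greatest in subgroups of about 50 men, and not a false claim that willingness overstates return. All tables, rates and correlations used here are illustrative, and all assume a yes/no cut of the Likert item that the article does not state. The point should be fixed before analysis, but it does not threaten the study.

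**What to change.** 1. State the cut that turns each Likert item into willing or not willing. The paired analysis cannot be run without it.
2. For each specimen, report the paired 2×2 table and the difference (willing minus returned) with a 95% CI for paired proportions and an exact McNemar test, overall and within race.
3. Keep Fisher's exact test only for between-category comparisons in which each man is counted once: return, or return among the willing. To ask whether the gap itself differs by characteristic, use a GEE logistic model with a measure-by-characteristic term.

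The cost is a change of wording and a little more analysis work. No new data are needed.

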### Theoretical Approach

Our study is grounded in the IMB model of HIV prevention [88] that describes pivotal constructs pertaining to health self-management [89]. Theoretical constructs of the IMB model will be applied to explore the acceptability and feasibility of self-collecting and potentially returning the 5 different types of specimens by MSM. *Information* will be assessed through a baseline survey in Phase 1, measuring pre-existing awareness of commercially available self-collection kits using questions adapted from our past research on rapid home HIV testing using oral fluid and finger-stick blood samples [90,91]. The survey will also assess participants’ knowledge of transmission and prevention of HIV and other STIs using the Sexually Transmitted Disease Knowledge Questionnaire (STD-KQ) [92]. *Motivation* will be examined through questions in the baseline survey on participants’ theoretical willingness to self-collect and return each type of specimen, expanding upon our previous study focusing exclusively on dried blood spot specimens [86] and by calculating the proportions of each type of specimen actually returned for laboratory testing. Depending upon their inclination, participants can choose to mail back all, some, or none of the 5 specimens. *Behavioral skills* will be measured by assessing the adequacy of returned specimens for current and future laboratory testing, thereby evaluating the ability of participants to self-collect and return useful specimens without supervision. Theoretical constructs of the IMB model will also be explored through qualitative in-depth interviews in Phase 2, which will focus on familiarity with the concept of biological specimen self-collection (information) and attitudes toward self-collecting and returning each type of specimen (motivation), as well as personal and logistical barriers encountered while performing study activities (behavioral skills).

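### The Discussion promises a comparison of perceived ability with specimen adequacy, but the Phase 1 Analytic Plan only summarises the two separately

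*Protocol article*

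**What the plan says.** **The promise** (Discussion, Principal Findings). "Our study will fill a critical gap in knowledge regarding feasibility by comparing the theoretical willingness and perceived ability to self-collect" each specimen type "with the proportions of specimens actually returned and their adequacy for laboratory testing, respectively". The closing adverb fixes two pairs: willingness with return, and perceived ability with adequacy.

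**The plan** (Phase 1 Analytic Plan). Under Motivation, the proportions returned are to be "compared with theoretical willingness using Fisher exact tests across categories of selected characteristics". Under Behavioral skills, item 1 says that frequency distributions of "perceived ability to self-collect and return each of the 5 different types of biological specimens will be plotted". Item 2 calculates "Proportions of each type of returned specimen that are deemed adequate for actual laboratory testing", or for potential drug-level testing in the case of hair. No item relates the two.

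**The measurements.** The baseline survey asks each participant about his intentions for each specimen type, "as well as their confidence to complete these activities using simple step-by-step written instructions" (Phase 1 Procedures). Everyone who completes that survey is sent a box. Return is voluntary and carries no incentive. Laboratory results are connected to participants through the box ID. The Discussion acknowledges that adequacy can be assessed only for specimens that come back.

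**The concern.** One of the two comparisons that the article presents as its contribution on feasibility has no matching analysis. The question is whether men who feel able to self-collect go on to produce a usable specimen. That concerns pairs of values within the same man. The plan gives two separate distributions: confidence in all baseline completers, and adequacy in the self-selected specimens that were mailed.

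The Theoretical Approach section puts the behavioural-skills construct at the level of participants, since adequacy is assessed "thereby evaluating the ability of participants to self-collect and return useful specimens without supervision". That sentence does not itself promise a comparison with perceived ability, but it shows why the participant level matters. If the plan is followed as written, the report could describe how confident the men were and how good the returned specimens were. It could not say whether the confident men were the ones who succeeded.

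**Working it through.** The documents give no figure to reproduce. The check has two parts.

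**1. Text against text**

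| Pair named in the Discussion | Step in the Phase 1 Analytic Plan |
|---|---|
| Willingness and return | Compared, with a named test (Motivation, item 2) |
| Perceived ability and adequacy | First plotted, second calculated; no comparison (Behavioral skills, items 1 and 2) |

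Phase 1 Outcomes likewise lists perceived ability and adequacy as two separate outcomes. No other section plans their comparison.

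**2. What the planned summaries can say**

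*Among all men sent a box.* The 100 men come from the protocol. The rest is assumed for illustration for one specimen type: 80 confident at baseline (so 20 not confident), 50 returned, 40 of those adequate. The cut of the Likert item into confident and not confident is also an assumption.

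The plan would report 80% confident, 50% returned, and 40/50 = 80% of returned specimens adequate. Let x be the number of adequate specimens that come from confident men.

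- Lower bound: the 20 men who were not confident can supply at most 20 adequate specimens, so x ≥ 40 − 20 = 20.
- Upper bound: x ≤ 40.
- Share of confident men with a usable specimen: 20/80 = 25% to 40/80 = 50%.
- Matching share of the other men: (40 − 20)/20 = 100% at the lower bound and (40 − 40)/20 = 0% at the upper.
- Difference, confident minus not confident: 25 − 100 = −75 points to 50 − 0 = +50 points.

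*Among returners only.* Suppose, more generously than the plan provides, that the confident proportion p among returners of a specimen type were also reported, together with the adequate proportion a. The joint proportion j must satisfy max(0, p + a − 1) ≤ j ≤ min(p, a). The difference in adequacy is j/p − (a − j)/(1 − p).

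| p (assumed) | a (assumed) | range of j | Difference in adequacy, confident minus not confident |
|---|---|---|---|
| 0.80 | 0.85 | 0.65 to 0.80 | −18.75 to +75 points |
| 0.70 | 0.90 | 0.60 to 0.70 | −14.3 to +33.3 points |
| 0.60 | 0.70 | 0.30 to 0.60 | −50 to +75 points |

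In every row the interval contains zero. The separate summaries do not settle the direction of the association, let alone its size.

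**The case against.** The best defence is that the Discussion sentence does not ask for a participant-level analysis. It can be read as an aggregate comparison across five specimen types, and the plan supplies each quantity that this would need. The Background defines feasibility as return and adequacy, and both are planned for each specimen type. Neither Aim 1 nor the outcomes list names confidence against adequacy as a question. The article is condensed, and the study is exploratory.

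Part of this stands. An informal side-by-side reading is possible, and nothing more formal than description is called for. The appeal to a fuller document is weaker: the article spells out the sister comparison in the same section and then states a different, purely descriptive treatment for this pair. The mismatch lies in what the text says.

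Four stronger readings are tempting and are not supported:

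- *A reader might infer that the report would suggest perfect agreement* (80% confident beside 80% adequate in the example). The return proportion is also planned, so readers would see that only 40 usable specimens came from 100 men.
- *A reader might infer that men who mailed nothing, or failed, vanish after the ability plot.* Inadequate returns are in the adequacy denominator. Non-returners count in the return proportion, their reasons are tabulated, and the posttest survey asks them again about perceived ability.
- *A reader might infer that the theoretical constructs are never related to behaviour.* Willingness is compared with actual return, and the Phase 2 interviews are sampled by return status.
- *A reader might fault the list of characteristics for leaving out kit awareness and the knowledge score.* The list is introduced as examples, so this is no error.

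It is also fair to object that non-return may reflect unwillingness rather than inability, and the article's framework places return under Motivation. Any remedy must keep the two apart.

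**Conclusion.** The point holds as a mismatch between stated purpose and stated analysis. A comparison of perceived ability with adequacy is promised, and the plan gives only separate summaries on different denominators. Read with the return proportion, these bound the answer without giving it: 25% to 50% of confident men with a usable specimen in the example, with the direction of the association undetermined. The figures rest on assumed counts and an assumed cut of the Likert item. The conclusion that the direction stays open held in every scenario tried. The mismatch leaves one stated question unanswered at participant level. It does not undermine the return and adequacy proportions, which are the main feasibility results. It is worth correcting before analysis.

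**What to change.** In the Phase 1 Analytic Plan, under Behavioral skills, add for each specimen type a descriptive cross-tabulation of baseline perceived ability by a three-level outcome (not returned, returned inadequate, returned adequate) among all men sent a box. Report the adequate proportion by confidence level, with confidence intervals, on two denominators: returners, and all men sent a box. Giving both keeps non-return from being read as inability. State how the Likert responses are grouped. No test is needed.

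The cost is a short change of wording and five small tables from data already collected and linked by box ID. The drawback is precision in the group who were not confident. As a rough guide with the assumed split and a proportion of 50%, the 95% half-width is 1.96 × √(0.25/20) ≈ 22 points for 20 men, against 1.96 × √(0.25/80) ≈ 11 points for 80. It would be wider again among returners only.

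If the team prefers not to add the tables, the Discussion sentence should be narrowed to an aggregate, descriptive comparison of perceived ability with adequacy. That reconciles the text but gives up the participant-level question.
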